### Primary, secondary, exploratory, and safety endpoints

Regarding the significance of achieving complete remission (CR) or ICR I, a decrease in urine protein level has been reported to be related to an improvement in prognosis [2]. Therefore, it is important to ensure that the patients achieve CR or ICR I as early as possible. In the Japanese guidelines, the evaluation of treatment effects after 1 or 6 months is considered a criterion for deciding the treatment strategy [5]. In contrast, it is known that B cells are depleted for at least 6 months by the administration of 1,000 mg rituximab via intravenous infusion every 2 weeks for two doses (days 1 and 15) for refractory pemphigus vulgaris and pemphigus foliaceus [10]. Therefore, week 26 (month 6) from the start of treatment was set as the point of evaluation to confirm the remission effect of rituximab. Accordingly, the percentage of patients achieving ICR I (criteria shown in Table 1) by week 26 of rituximab administration was defined as the primary endpoint.

The secondary endpoints included: 1) percentage of patients who achieved CR, ICR I, ICR II, NR, or PR (each criterion is shown in Table 1) at each assessment time point; 2) duration before achieving CR, ICR I, ICR II, or PR; 3) urine protein/creatinine ratio; 4) estimated glomerular filtration rate; 5) B cell (CD19-positive and CD20-positives) counts; 6) expression of human anti-chimeric antibodies; and 7) serum rituximab levels. The safety endpoints included adverse events, vital signs, oxygen saturation, and laboratory test results.

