## Abstract

In Japan, corticosteroid monotherapy has traditionally been recommended as the first-line therapy for membranous nephropathy with nephrotic syndrome. In contrast, except for Japan, rituximab is recommended as the first-line therapy for membranous nephropathy with nephrotic syndrome. This clinical trial aimed to verify the efficacy and safety of the intravenous administration of rituximab without steroids or immunosuppressants as an induction therapy in Japanese patients with idiopathic membranous nephropathy and nephrotic syndrome. This was a multicentre (15 in Japan), placebo-controlled, randomized, double-blind, parallel-group comparative study. A total of 88 patients diagnosed with idiopathic membranous nephropathy and nephrotic syndrome were randomly allocated to rituximab and placebo groups in a 1:1 ratio; rituximab 1,000 mg or placebo IV infusion was administered every 2 weeks for two doses in a double-blinded manner. The primary endpoint was the percentage of patients achieving less than 1.0 g/g creatinine in urine protein/creatinine ratio in random urine at 26 weeks after the first administration of rituximab or placebo. This study was approved by the institutional review boards and conducted in accordance with the Good Clinical Practice guidelines. This study was registered at ClinicalTrials.gov, NCT05914155 and the Japan Registry of Clinical Trials, jRCT2041230037 on 13 June 2023.

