## Materials and Methods

### Objective, overall design, and framework

The primary objective of this clinical study was to confirm the efficacy and safety of intravenous rituximab in patients diagnosed with idiopathic membranous nephropathy with nephrotic syndrome. The primary endpoint was the percentage of patients achieving incomplete remission type I (ICR I) with the urine protein/creatinine ratio <  1.0 g/g creatinine. The criteria for treatment effects are shown in Table 1.

**Table 1 pone.0320070.t001:** Criteria for treatment effects.

CR	Urine protein/creatinine ratio < 0.3 g/g creatinine
ICR I	0.3 g/g creatinine ≤ Urine protein/creatinine ratio < 1.0 g/g creatinine
ICR II	1.0 g/g creatinine ≤ Urine protein/creatinine ratio < 3.5 g/g creatinine
NR	Urine protein/creatinine ratio ≥ 3.5 g/g creatinine
PR	Decrease in urine protein/creatinine ratio from base line ≥ 50%, and urine protein-creatinine ratio 0.3 to 3.5 g/g creatinine

The treatment effect will be evaluated using random urine samples at each point after the administration of the investigational drugs.

CR: Complete Remission, ICR I: Incomplete Remission Type I, ICR II: Incomplete Remission Type II, NR: No Response, PR: Partial Response

The PRIME study is a placebo-controlled, randomized, double-blind, parallel-group, comparative study, followed by an open-label, single-arm study. In the double-blind phase of this trial, patients will be randomly allocated to rituximab and placebo groups in a 1:1 ratio, and rituximab 1,000 mg or placebo infusion will be administered every 2 weeks for two doses in a double-blinded manner. However, if patients with incomplete remission type II (ICR II) or no response (NR) until the evaluation at week 26 in the double-blind phase wish to move to the open-label phase, and the investigator considers the move necessary, the patient may move to the open-label phase and receive intravenous infusion of rituximab 1,000 mg every 2 weeks for two doses. This move will be performed after the eligibility criteria for re-administration is confirmed. An outline of this clinical trial is shown in Fig 1.

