### Sample size and statistical analysis

In a cohort study on idiopathic membranous nephropathy by Nagoya University (Nagoya cohort), there were 14 out of 64 (21.9%) patients with membranous nephropathy with equivalent to nephrotic syndrome using no steroids or immunosuppressants (data not disclosed). Therefore, the percentage of patients achieving ICR I 6 months after the initial treatment in the placebo group was expected to be approximately 22% in this study. In addition, as there have been no prior clinical studies on rituximab monotherapy in Japan, the expected efficacy of rituximab is presumed to be 52%. For 80% power with a two-sided significance level of 5%, 40 cases per group were required. Estimating discontinuation/dropout to be approximately 10%, the target number of cases was defined as 88 in the two groups.

We treated this as a safety analysis set in which patients were enrolled for the double-blind phase and received at least one dose of the investigational drug. The primary analysis of the primary and secondary endpoints will be conducted in the full analysis set, with patients in the safety analysis set excluding patients with significant violations of the protocol (not providing consent or significant violation of the trial procedure) and with no data after administration of the investigational drug.

For analysis of the primary endpoint, the percentage of patients achieving ICR I at week 26 and 95% confidence intervals were calculated. The 95% confidence intervals were calculated using the Clopper-Pearson method. A Chi-square test was performed to compare the two groups when analyzing the double-blind phase. For secondary analyses, the percentages of patients achieving ICR-I before weeks 4, 8, and 16 were calculated in a similar manner. The duration before achieving CR, ICR I, ICR II, or PR was estimated using the Kaplan-Meier method. Summary statistics of urine protein/creatinine ratio, eGFR, B cells, and pharmacokinetics parameter were calculated for continuous variables. All statistical analyses were performed using SAS (SAS Institute Inc., Cary, NC, USA) and Phoenix WinNonlin software (Certara, USA). All statistical tests were two-sided, and P-values < 0.05 were considered statistically significant.

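### The article gives two incompatible primary endpoints: every patient below 1.0 g/g, or only the Table 1 ICR I band of 0.3 to below 1.0 g/g, which leaves out complete remission

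*Protocol article*

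**What the plan says.** All places are in the protocol article.

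- **Abstract.** The primary endpoint is "the percentage of patients achieving less than 1.0 g/g creatinine in urine protein/creatinine ratio in random urine at 26 weeks". There is no lower bound, so CR is included.
- **Objective, overall design, and framework.** "The primary endpoint was the percentage of patients achieving incomplete remission type I (ICR I) with the urine protein/creatinine ratio" below 1.0 g/g creatinine. The label is ICR I, but the threshold attached to it has no lower bound.
- **Table 1, same section.** ICR I is "0.3 g/g creatinine ≤ Urine protein/creatinine ratio < 1.0 g/g creatinine". CR is a ratio below 0.3 g/g. CR, ICR I, ICR II and NR do not overlap.
- **Primary, secondary, exploratory, and safety endpoints.** "the percentage of patients achieving ICR I (criteria shown in Table 1) by week 26 of rituximab administration was defined as the primary endpoint". The same section gives the reason for the choice: "it is important to ensure that the patients achieve CR or ICR I as early as possible".
- **Sample size and statistical analysis.** "For analysis of the primary endpoint, the percentage of patients achieving ICR I at week 26 and 95% confidence intervals were calculated". CR is not mentioned. The ICR I percentages for weeks 4, 8 and 16 are to be handled in a similar manner, and "The duration before achieving CR, ICR I, ICR II, or PR was estimated using the Kaplan-Meier method".

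No sentence says that ICR I includes CR for the primary analysis.

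**The concern.** The endpoint section takes its definition from Table 1, and the analysis section uses the same label. Anyone programming the response variable from those two places would code a patient at 0.2 g/g as not achieving ICR I, so the best outcome would count as a non-response. Someone working from the Abstract would code the same patient as a success.

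Three things are at stake.

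- **The primary result.** The two codings can give different answers. If both definitions are still on paper at unblinding, the choice between them can look driven by the data. The article hopes that the results will support marketing approval.
- **The treatment contrast.** If rituximab produces more complete remissions than placebo, the literal band removes more successes from the rituximab arm.
- **The planning rates.** The 22% for placebo is labelled ICR I, but the article does not say which outcome the 14 of 64 cohort patients reached. The 52% is called only expected efficacy. Until one definition is fixed, nobody can check that the sample size belongs to the endpoint.

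The ICR I percentages at weeks 4, 8 and 16 carry the same ambiguity. So do the times to ICR I and ICR II.

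**Working it through.** **Step 1. The two definitions applied to one patient in week 26.**

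| Ratio (g/g) | Table 1 category | Abstract, and threshold in design section | Endpoint and analysis sections read with Table 1 |
|---|---|---|---|
| 0.2 | CR | responder | non-responder |
| 0.6 | ICR I | responder | responder |
| 2.0 | ICR II | non-responder | non-responder |

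The definitions differ only for patients in CR.

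**Step 2. Reproduce the planned sample size.** Inputs from the sample size section: p1 = 0.22 (14/64 = 21.9%), p2 = 0.52, two-sided 5%, 80% power, chi-square test. With mean rate p = (0.22 + 0.52)/2 = 0.37, pooled variance and no continuity correction:

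n = {1.960·√[2p(1−p)] + 0.842·√[p1(1−p1) + p2(1−p2)]}² / (p2−p1)²
= (1.960 × 0.6828 + 0.842 × 0.6490)² / 0.30² = 39.5, so 40 per group.

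This agrees with the article, and 80 × 1.1 = 88. Power at 40 per group:

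Φ{[(p2−p1)·√40 − 1.960·√(2p(1−p))] / √[p1(1−p1) + p2(1−p2)]}
= Φ[(1.8974 − 1.3383)/0.6490] = Φ(0.861) = 80.6%.

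Exact power of the chi-square test is 80.9%. The arithmetic of the plan is sound; the fault lies in the definition.

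**Step 3. Effect of scoring CR as non-response.** The article gives no CR rates, so the CR shares below are assumptions. If 22% and 52% are totals below 1.0 g/g, the ICR I rates are 22% minus placebo CR and 52% minus rituximab CR. The power formula of step 2, with 40 per arm, gives:

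| Assumed CR, placebo / rituximab (points) | ICR I alone | Power |
|---|---|---|
| 0 / 0 | 22% v 52% | 80.6% |
| 2 / 5 | 20% v 47% | 73.4% |
| 3 / 10 | 19% v 42% | 61.1% |
| 5 / 15 | 17% v 37% | 52.2% |
| 5 / 5 | 17% v 47% | 83.3% |

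Exact chi-square power agrees within 1 point. The direction depends on the difference in CR between arms. A CR excess on rituximab lowers power. Equal shares leave the 30-point difference intact and raise power slightly.

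**Step 4. The other reading of the planning rates.** If 22% and 52% already mean ICR I alone, the literal band has the planned 80.6% power.

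**Step 5. What the rest of the article indicates.** The rationale names CR or ICR I as the goal and leads directly into the endpoint definition. Entry to the open-label phase is limited to ICR II or NR (design section, re-administration criteria, and registration section), so a patient in CR is grouped with ICR I as not needing re-treatment. Both point to CR plus ICR I. Against this, the first secondary endpoint lists CR and ICR I separately, each by its Table 1 criterion. If ICR I also means ICR I or better, one label with one table reference carries two meanings in the same section.

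**The case against.** The strongest reply is that the intent is plain. The Abstract and the design section both use below 1.0 g/g, the rationale says CR or ICR I, and the open-label rule treats the two alike. Achieving ICR I can then be read as crossing the 1.0 g/g threshold, and the full protocol and analysis plan, which are not shown, may code it so. The part about intent stands. A reader might infer that the trial will in fact score complete remissions as failures. The documents do not support that: it is the literal consequence of two sections, contradicted by two others. The contradiction remains all the same, because the sections that define and analyse the endpoint are the ones that point to the exclusive band.

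A reader might also infer that power is bound to fall. It is not. That needs both planning rates to be totals below 1.0 g/g and a CR excess on rituximab. The excess is plausible for an effective drug, but its size is unknown. Larger assumed gaps give lower power (34% at 5/20 points), but nothing in the article supports a gap of that size at week 26. Its limitations paragraph says that an earlier rituximab trial saw the more pronounced fall in proteinuria after 6 months.

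Finally, a reader might infer that a patient who goes straight to CR is censored in the Kaplan-Meier analysis of time to ICR I. The article states no event or censoring rule, and such a rule commonly sits in the analysis plan. What can be said is that exclusive bands leave the event undefined for such a patient.

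**Conclusion.** The point holds as a contradiction in the definition of the primary endpoint. Two places count all patients below 1.0 g/g, and two places, read with Table 1, count only 0.3 to below 1.0 g/g. The internal evidence favours CR plus ICR I as the intended endpoint, but no defining or analysis sentence says so. It must be settled before unblinding, because it decides who is a responder in the primary comparison.

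The size is conditional. With 40 per arm, 22% and 52% as totals below 1.0 g/g, and assumed CR shares from 2/5 to 5/15 points, literal scoring gives 73% to 52% power. Equal shares of 5 points give 83%. If the planning rates are for ICR I alone, the literal band keeps 80.6%. If the endpoint is below 1.0 g/g and the rates refer to it, the sample size needs no change. These figures illustrate what depends on the wording; they do not forecast the trial's power.

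**What to change.** 1. In the design, endpoint and analysis sections, state the primary endpoint as CR or ICR I, i.e. urine protein/creatinine ratio below 1.0 g/g creatinine. Use the same wording for the ICR I percentages at weeks 4, 8 and 16.
2. Confirm that 22% (14/64) and 52% refer to that outcome. If they do, 40 per group stands. If either refers to ICR I alone, redo the calculation with rates for the stated endpoint.
3. For time to ICR I and time to ICR II, state that reaching a better category counts as the event. Leave PR as Table 1 defines it: it overlaps ICR I and ICR II, so it has no place in a single ordering.
4. Keep the exclusive Table 1 bands for the by-visit table of categories.

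The cost is a wording amendment, and a matching check of the analysis plan and response coding, made and dated before unblinding. No visits, measurements or patients are added. Only if step 2 shows that the rates belong to a different outcome does the sample size need another look.

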### Sample size and statistical analysis

In a cohort study on idiopathic membranous nephropathy by Nagoya University (Nagoya cohort), there were 14 out of 64 (21.9%) patients with membranous nephropathy with equivalent to nephrotic syndrome using no steroids or immunosuppressants (data not disclosed). Therefore, the percentage of patients achieving ICR I 6 months after the initial treatment in the placebo group was expected to be approximately 22% in this study. In addition, as there have been no prior clinical studies on rituximab monotherapy in Japan, the expected efficacy of rituximab is presumed to be 52%. For 80% power with a two-sided significance level of 5%, 40 cases per group were required. Estimating discontinuation/dropout to be approximately 10%, the target number of cases was defined as 88 in the two groups.

We treated this as a safety analysis set in which patients were enrolled for the double-blind phase and received at least one dose of the investigational drug. The primary analysis of the primary and secondary endpoints will be conducted in the full analysis set, with patients in the safety analysis set excluding patients with significant violations of the protocol (not providing consent or significant violation of the trial procedure) and with no data after administration of the investigational drug.

For analysis of the primary endpoint, the percentage of patients achieving ICR I at week 26 and 95% confidence intervals were calculated. The 95% confidence intervals were calculated using the Clopper-Pearson method. A Chi-square test was performed to compare the two groups when analyzing the double-blind phase. For secondary analyses, the percentages of patients achieving ICR-I before weeks 4, 8, and 16 were calculated in a similar manner. The duration before achieving CR, ICR I, ICR II, or PR was estimated using the Kaplan-Meier method. Summary statistics of urine protein/creatinine ratio, eGFR, B cells, and pharmacokinetics parameter were calculated for continuous variables. All statistical analyses were performed using SAS (SAS Institute Inc., Cary, NC, USA) and Phoenix WinNonlin software (Certara, USA). All statistical tests were two-sided, and P-values < 0.05 were considered statistically significant.

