### Registration and randomisation

The investigators obtained written informed consent from all eligible patients, who were willing to enroll in the study. After all inclusion and exclusion criteria were confirmed, the investigators registered all items required for enrollment/eligibility confirmation on the electronic data capture system. Patients confirmed to eligible were randomly assigned to the rituximab or placebo group at a ratio of 1:1 in the minimization method according to the following factors: their urine protein/creatinine ratio (<5.0 g/g creatinine/≥5.0 g/g creatinine) at the time of the screening, and use of angiotensin converting enzyme inhibitor or angiotensin receptor blocker at the obtainment of consent (yes/no).

The investigators obtained written informed consent from all eligible patients who showed ICR II or NR until the time of evaluation at week 26 in the double-blind phase, met the re-administration criteria, and wished to have a re-challenge with rituximab. Subsequently, the patients were then registered on the electronic data capture system.

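### Allocation is minimised on screening urine protein/creatinine ratio and ACE inhibitor/ARB use, but the stated primary test is an unadjusted Chi-square: valid, but conservative to the extent that those factors are prognostic

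*Protocol article*

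**What the plan says.** Under Registration and randomisation, the Protocol article allocates patients "at a ratio of 1:1 in the minimization method according to the following factors". The factors are the screening urine protein/creatinine ratio, cut at 5.0 g/g, and use of an ACE inhibitor or ARB at consent.

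Under Sample size and statistical analysis, the primary analysis reports the percentage of responders at week 26 with a 95% interval: "The 95% confidence intervals were calculated using the Clopper-Pearson method". The between-group comparison is then fixed: "A Chi-square test was performed to compare the two groups when analyzing the double-blind phase". Neither minimisation factor appears in that section as a stratum or covariate.

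The same section gives the planning figures: a response rate that "in the placebo group was expected to be approximately 22% in this study", 52% on rituximab, and "For 80% power with a two-sided significance level of 5%, 40 cases per group were required". With dropout, "Estimating discontinuation/dropout to be approximately 10%, the target number of cases was defined as 88 in the two groups".

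**The concern.** Minimisation removes most of the chance imbalance between arms on the chosen factors. If those factors predict response, the true sampling variance of the difference in response rates falls. The unadjusted Chi-square still uses the total binomial variance, as if the imbalance could occur. Its standard error is then too large and its p-value too high.

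The first factor is the one to consider. The endpoint is a ratio below 1.0 g/g and entry requires at least 3.5 g/g. A patient entering at 3.5 g/g must fall by more than 1 − 1/3.5 = 71%; at 5.0 g/g by more than 1 − 1/5 = 80%; at 10 g/g by more than 1 − 1/10 = 90%. A link between this factor and response is therefore plausible, and the sponsor thought it important enough to balance on.

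At stake is efficiency in a confirmatory trial of modest size, intended to support marketing approval. The false-positive rate is not at risk.

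**Working it through.** **1. Reproduce the plan's figure.** Inputs from Sample size and statistical analysis: p0 = 0.22, p1 = 0.52, two-sided α = 0.05, power 80%. Mean rate = 0.37.

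n per group = [1.96 × √(2 × 0.37 × 0.63) + 0.8416 × √(0.22 × 0.78 + 0.52 × 0.48)]² / 0.30²
= [1.3383 + 0.5462]² / 0.09 = 39.5, so 40.

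Power at 40 per group is 0.806 by the same formula, and 0.809 by exact binomial enumeration of the uncorrected Chi-square. Then 80 × 1.1 = 88. The sample size and the stated unadjusted test agree with each other.

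**2. Why the test turns conservative.** Take an assumed odds ratio of 0.1 for a ratio of 5.0 g/g or above, half the patients above the cut, and an overall rate of 22% in both arms. The stratum rates are then about 38% and 6%.

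- Variance per patient used by the Chi-square: 0.22 × 0.78 = 0.1716.
- Variance when the strata are balanced: 0.5 × 0.38 × 0.62 + 0.5 × 0.06 × 0.94 = 0.1460.
- Ratio: 0.1460 / 0.1716 = 0.851. The nominal 1.96 acts as 1.96 / √0.851 = 2.12, so the actual two-sided error is about 3.4%.

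**3. Simulation.** The protocol article gives no prognostic strength, factor prevalence or minimisation probability, so all are assumed: 80 patients; 60% at 5.0 g/g or above; 70% on an ACE inhibitor or ARB; biased-coin probability 0.8; overall rates 22% v 52% for power and 22% in both arms for type I error; 6,000 trials per scenario. CMH is the Cochran-Mantel-Haenszel test over the four strata.

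| Odds ratio (≥5.0 g/g; ACE inhibitor/ARB) | Power, Chi-square | Power, CMH | Change (points) | Type I, Chi-square | Type I, CMH |
|---|---|---|---|---|---|
| 1; 1 | 82.3% | 81.1% | −1.2 | 5.5% | 5.2% |
| 0.5; 1 | 81.6% | 81.1% | −0.5 | 4.7% | 4.8% |
| 0.33; 1.5 | 81.3% | 82.1% | +0.8 | 4.8% | 5.1% |
| 0.2; 2 | 82.4% | 85.0% | +2.5 | 4.0% | 5.2% |
| 0.1; 2 | 83.8% | 89.0% | +5.2 | 3.5% | 5.0% |

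Changes are taken from unrounded figures. The Monte Carlo standard error is about √(0.8 × 0.2 / 6000) = 0.5 point for a power and √(0.05 × 0.95 / 6000) = 0.3 point for a type I error. The 5.5% in the first row is therefore compatible with the nominal 5%.

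**4. Sensitivity to the assumptions.** A second set of runs used half the patients at 5.0 g/g or above, a common null rate of 37% and 5,000 trials per scenario. The power gains were 0.8, 2.0 and 4.7 points at odds ratios 0.33, 0.2 and 0.1, with Chi-square type I error of 4.7%, 3.8% and 2.8%. Across all runs, Chi-square type I error was 3.6% to 4.0% at an odds ratio of 0.2 and 2.5% to 3.5% at 0.1, while CMH stayed near 5%.

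**The case against.** The strongest defence is that nothing here is broken. The sample size was computed for the test that is planned, and in every scenario the unadjusted Chi-square has at least 81% power. A reader might infer that the trial falls short of its planned power, or that ignoring the minimisation factors inflates the false-positive rate. Neither is supported: any loss is power that could have been had above the target, and the error moves in the safe direction.

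The gain also depends on an input that the article does not give. It is nil or slightly negative for weak factors. The +5 points needs an odds ratio of 0.1 across one cut, among patients who all enter at 3.5 g/g or more. With half above the cut, that means about 38% v 6% responding on placebo and 78% v 26% on rituximab. Nothing in the article supports so steep a gradient. This stands, and it is why the claim is conditional.

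A reader might also infer that no interval for the treatment effect is planned, since Clopper-Pearson is a one-proportion method. The article does not say those are the only intervals, and a condensed article may leave an interval for the difference to the full protocol or SAP. That inference should not be drawn. Nor does the article propose judging the effect by whether the arm intervals overlap.

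The defence does not remove the mismatch. The unadjusted test is a stated choice, and so are the minimisation factors that it sets aside.

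**Conclusion.** The point holds as a matter of efficiency and coherence between allocation and analysis; it is not a validity error. The stated test controls type I error and meets the planned 80%. If screening urine protein is strongly prognostic (assumed odds ratio 0.2 to 0.1), actual type I error drops to roughly 4.0% down to 2.5%, and a stratified test would add about 2 to 5 points of power. At an odds ratio of 0.5 the change is about nil, and with no prognostic value it is about −1 point. Confidence is high in the mismatch and in the direction of the effect. The size is uncertain, because it rests on assumed odds ratios, prevalences and a minimisation probability that the article does not state. An inexpensive change with a small, bounded downside is worth making.

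**What to change.** Before unblinding:

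- Make the primary test a Cochran-Mantel-Haenszel test stratified by the two minimisation factors, as used at allocation.
- Prespecify a pooling rule for sparse strata, for example collapsing over ACE inhibitor/ARB use first. Under the prevalences assumed above, the smallest stratum would hold about 0.4 × 0.3 × 80 = 9.6 patients, so the rule may well be needed.
- Name the matching stratified risk difference with its 95% confidence interval as the effect estimate.
- Keep the unadjusted Chi-square as a sensitivity analysis and the Clopper-Pearson arm intervals as description.

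The cost is wording only: no new data and no change to the 88 patients. The downside is up to about 1 point of power if neither factor is prognostic. This also changes the primary test of a trial whose main design the regulator has agreed, so the sponsor may need to notify the regulator.
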